### Imputation of missing data

Multiple imputations will be used for subjects with missing primary outcome data. Variables will be included in the multiple imputations, including the baseline 24-h UP, 24-h UP every 4 weeks, HbA1c, age, sex, and the characteristics and possible influencing factors of 24-h UP change. The missing data will be imputed five times. For missing secondary and safety outcomes, the results will be analyzed according to the actual data; the missing data will not be imputed nor will the model be adjusted. Furthermore, we will conduct a per-protocol analysis that excluded those with missing outcome data.

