**Methods:**

This trial is a 24-week, randomized, multicentric, double-blinded, double-dummy clinical trial. A total of 120 patients with DKD will be equally and randomly divided into two groups: SZF+ irbesartan simulator or irbesartan + SZF simulator. The 24-h urinary protein change from baseline to week 24 is the primary outcome measure. The secondary outcome measures include serum creatinine, estimated glomerular filtration rate, urinary albumin excretion rate, improvement in traditional Chinese medicine symptoms, fasting blood glucose, 2-h postprandial plasma glucose, hemoglobin A1c, cholesterol, triglycerides, high density lipoprotein, low density lipoprotein, blood pressure, albumin to creatinine ratio, and the Audit of Diabetes-Dependent Quality of Life 19. Our recruitment began in May 2015; currently, we have recruited 100 participants, with a designed maximum sample size of 120. The interim results were reviewed at *N* = 60, and continuing recruitment was recommended. This statistical analysis plan includes our approach to missing data imputation, primary and secondary outcomes analyses, and safety endpoints.

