### Randomization and blinding

Eligible patients will be randomized in a 1:1 allocation ratio using a central permuted block randomization procedure (block size 4) with block sizes. The groups will include the TCM group, which will receive SZF and stimulated irbesartan, and the Western medicine group, which will receive SZF simulation agents and irbesartan capsules. Using the PROC PLAN process statement of SAS 9.4 (SAS/STAT Software 9.4, SAS Institute, Inc., Cary, NC, USA), a random arrangement (random coding table) of 120 subjects will be generated according to the number of seeds. The Institute of Basic Research in Clinical Medicine of the China Academy of Chinese Medical Sciences provides the random arrangement, 24-h emergency code break, and medical information. Participants, investigators, and statisticians will be blinded to treatment assignments.

SZF drugs and SZF simulators have identical shape, smell, and color, which were consistent when dissolved in water. Irbesartan capsules and simulators had consistent scent and appearance when the capsule was opened.

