## Analysis methods

### Outcome measure analyses

#### Primary outcome analyses

The primary analysis will be conducted in the FAS and PPS. The change in 24-h UP (mg/24 h) is the primary outcome. The distribution and changes of 24-h UP at weeks 0, 4, 8, 12, 16, 20, and 24 of medication will be described. Intra- and inter-group comparisons will be made. The distributions of qualitative judgments of 24-h UP at weeks 4, 8, 12, 16, 20, and 24 will be described and compared between groups. The baseline 24-h UP is essential to assess the progression of UP; therefore, analysis of covariance (ANCOVA) will be performed to analyze the 24-h UP change from baseline to week 24, using baseline 24-h UP as a covariate. Interactions between site and group will also be tested.

Table 3 provides a reference for the qualitative determination of the variation. The efficiency rate will be calculated by summing the rate of clinical control, obvious therapeutic effect, and therapeutic effect (Table 4).

**Table 3 Tab3:** 24-h UP qualitative judgments classification standard

Qualitative judgment	Standard
Clinical control	24-h UP< 0.5 g
Obvious therapeutic effect	24-h UP reduction ≥ 50%
With therapeutic effect	24-h UP reduction ≥ 20%
Invalid	Fail to reach the standards above

**Table 4 Tab4:** Analysis of primary outcome

Time point	SZF, number, mean (SD)	Irbesartan, number, mean (SD)	Mean difference (95% CI)	***p*** value
Visit at	*n* = xx	*n* = xx		
Week 0	xx (xx)	xx (xx)	xx (xx to xx)	.xx
Week 4 ^a^	xx (xx)	xx (xx)	xx (xx to xx)	.xx
Week 8	xx (xx)	xx (xx)	xx (xx to xx)	.xx
Week 12	xx (xx)	xx (xx)	xx (xx to xx)	.xx
Week 16	xx (xx)	xx (xx)	xx (xx to xx)	.xx
Week 20	xx (xx)	xx (xx)	xx (xx to xx)	.xx
Week 24	xx (xx)	xx (xx)	xx (xx to xx)	.xx
Overall SZF effect^b^				.xx

^a,b^*p* values comparing between group differences at visit points post-randomization (a) and over the entire24-week trial (b: primary outcome)

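### The imputation variables named for missing 24-h urinary protein do not include randomised arm; used as named, they would shrink the SZF–irbesartan difference. Separately, five imputations add avoidable noise

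*Protocol article*

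**What the plan says.** All references are to the Protocol article.

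- **Imputation of missing data.** The method is stated as "Multiple imputations will be used for subjects with missing primary outcome data". The variables are given as "including the baseline 24-h UP, 24-h UP every 4 weeks, HbA1c, age, sex, and the characteristics and possible influencing factors of 24-h UP change". The number of imputations is fixed: "The missing data will be imputed five times". Arm and site are not named, and imputing by arm is not mentioned.
- **Primary outcome analyses.** The analysis is specified as "analysis of covariance (ANCOVA) will be performed to analyze the 24-h UP change from baseline to week 24, using baseline 24-h UP as a covariate", comparing the two groups. The section adds: "Interactions between site and group will also be tested". The outcome is measured every four weeks: "24-h UP at weeks 0, 4, 8, 12, 16, 20, and 24 of medication will be described".
- **Abstract, Methods, and Randomization and blinding.** "A total of 120 patients with DKD will be equally and randomly divided into two groups", and "Eligible patients will be randomized in a 1:1 allocation ratio", so 120/2 = 60 per arm.

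**The concern.** An imputation model should contain at least the terms of the analysis model it feeds. Here the term of interest, arm, is missing from the named variables. A model without arm predicts each missing week-24 value from a relationship pooled over SZF and irbesartan patients. Any part of the treatment effect not already visible in the patient's observed 24-h UP values is then lost from the imputed value.

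At stake is an understated treatment difference in the full analysis set, with a matching loss of power. Both grow with the share of missing week-24 values.

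**Working it through.** **Inputs from the article:** 60 per arm; visits at weeks 0, 4, 8, 12, 16, 20 and 24; ANCOVA on arm and baseline; two-sided alpha 0.05; m = 5 imputations.

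**Assumptions (the article gives no figures for these):** week-24 effect d = 0.5 SD; 10, 20 or 30% of week-24 values missing at random; between-visit correlation 0.6 throughout or 0.8 per visit step (autoregressive); effect building up linearly, at once, or late; patients last seen at week 0, 12 or 20.

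**Step 1: expected size.** Let q be the share missing in each arm, and r the share of d that a model without arm recovers through the observed visits. Then

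estimated/true = (1 − q) + q·r = 1 − q(1 − r).

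If only baseline was seen, r = 0 and the ratio is 1 − q: 0.90, 0.80 and 0.70 at 10, 20 and 30% missing.

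**Step 2: large-sample simulation of the same ratio.** Each range covers the three effect shapes and both correlation patterns.

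| Missing | No arm, last seen wk 0 | No arm, wk 12 | No arm, wk 20 | Arm included, all settings |
|---|---|---|---|---|
| 10% | 0.895–0.906 | 0.899–0.976 | 0.918–0.987 | 0.994–1.011 |
| 20% | 0.797–0.806 | 0.793–0.940 | 0.835–0.964 | 0.990–1.014 |
| 30% | 0.694–0.703 | 0.690–0.917 | 0.768–0.947 | 0.985–1.008 |

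The week-0 column agrees with 1 − q. The other columns show how far the four-weekly values help. At 20% missing, a ratio of 0.852 (linear effect, last seen week 12, correlation 0.6) gives r = 1 − 0.148/0.20 = 0.26. A ratio of 0.964 (immediate effect, last seen week 20, autoregressive) gives r = 1 − 0.036/0.20 = 0.82. With a late effect and patients last seen at week 12, nothing material is recovered.

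The shrinkage is therefore 4–21% at 20% missing and 5–31% at 30%. At 10% missing it is about 3–10% in 15 of the 18 settings and 1–2% in the other three.

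Two further simulations with 60 per arm and adjacent-visit correlation 0.77 agree in direction. Without arm, one gave ratios of 0.90–0.92, 0.80–0.85 and 0.72–0.76 at 10, 20 and 30% missing; the other gave 0.93–0.97, 0.84–0.95 and 0.78–0.89. With arm, both were about 1.0.

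**Step 3: 60 per arm, proper multiple imputation, Rubin's rules with small-sample degrees of freedom.** Linear effect, last seen week 12; 1,500 runs for m = 5 and 500 for m = 50.

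| Missing | m | Ratio without / with arm | Power without / with arm |
|---|---|---|---|
| 10% | 5 | 0.933 / 1.003 | 86% / 90% |
| 10% | 50 | 0.908 / 0.989 | 86% / 91% |
| 20% | 5 | 0.840 / 1.000 | 76% / 85% |
| 20% | 50 | 0.823 / 0.985 | 74% / 85% |
| 30% | 5 | 0.758 / 1.004 | 58% / 79% |
| 30% | 50 | 0.774 / 1.004 | 66% / 83% |

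Raising m does not remove the shrinkage. At 30% missing the two no-arm ratios differ by 0.774 − 0.758 = 0.016. Their simulation errors are 0.139/√1500/0.5 = 0.007 and 0.131/√500/0.5 = 0.012, which combine to √(0.007² + 0.012²) = 0.014. The lower power with m = 5 at 30% missing is a loss of precision, not a shift in the estimate.

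**Step 4: precision cost of five imputations.** Relative efficiency = 1/(1 + FMI/m), where FMI is the fraction of missing information. The standard error grows by √(1 + FMI/m) relative to unlimited imputations.

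| FMI | Efficiency, m = 5 | SE factor, m = 5 | Efficiency, m = 50 |
|---|---|---|---|
| 0.1 | 0.980 | 1.010 | 0.998 |
| 0.2 | 0.962 | 1.020 | 0.996 |
| 0.3 | 0.943 | 1.030 | 0.994 |
| 0.5 | 0.909 | 1.049 | 0.990 |

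**The case against.** **The list is open.** It ends in an unspecified category of factors that may affect the outcome, and treatment is an obvious candidate. A reader might infer that the plan excludes arm or pools the arms. The text does not say so, and this objection stands: the bias is conditional on arm being left out. But a category that can be filled later does not secure the one term the primary test needs.

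**The article is condensed.** A full SAP (version 2.0) exists and is not shown; it may name arm. That also stands. However, the article presents itself as the pre-determined analysis plan, lists imputation within its scope, and fixes both variables and a number of imputations. The point concerns what it fixes.

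**The four-weekly values repair the effect.** They do so in part, as Step 2 shows, and best when dropout is late and the effect appears early.

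**The full analysis set may leave few patients to impute.** Its definition is unclear. If it requires a post-treatment primary value, the week-0 column drops out, but the week-12 column reaches the same lower end.

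**The per-protocol analysis avoids imputation.** It does, by excluding patients with missing outcomes. It answers for a different set of patients and does not correct the full-analysis-set estimate.

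**Site is not named either.** A reader might infer that imputation should be done within arm with site terms, because a site-by-group interaction is tested. With 11 centres, 120/11 is about 11 patients per centre, and a within-arm model would have at most 60 patients. That is too thin to recommend.

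**Conclusion.** The concern holds in conditional form. Arm is not among the named imputation variables. If those variables alone were used, the SZF–irbesartan difference would shrink by about 3–10% at 10% missing (1–2% in the mildest settings), 4–21% at 20%, and up to about 30% at 30%. With arm included the bias is about zero. The direction does not depend on the assumed inputs; the size does. Effect size, correlation, effect shape, dropout rate and dropout timing are all assumptions, with data missing at random.

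Three stronger readings are not supported:

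- **That the primary estimate is biased as planned.** The document leaves arm unspecified.
- **That five imputations contribute to the pull towards zero.** They cost about 1–5% in standard error for FMI of 0.1 to 0.5 and make the p-value partly dependent on the seed, with no bias in either direction.
- **That the trial would falsely establish equivalence with irbesartan.** The Overall principles section tests a null of no difference, and the article plans no equivalence or non-inferiority conclusion. The formal cost is power, although a shrunken difference could still invite an informal reading of similarity.

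**What to change.** Amend the imputation section, in a dated change before unblinding, to state that:

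1. The imputation model contains randomised arm, together with baseline and all observed 24-h UP visits, HbA1c, age and sex. Arm can be entered as a blinded code, so the statisticians stay blinded.
2. The closing open-ended category is replaced by a closed list of any further variables.
3. Imputation is done on the scale that the ANCOVA uses, so that the two models agree.
4. About 50 imputations are used, with the seed recorded.

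The cost is wording and computing time. No data collection, visit or sample-size change is involved.

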## Study methods

### Trial design

The SZF clinical trial will be conducted in 11 centers and will recruit 120 patients with macroalbuminuria secondary to DKD. In the protocol, we specified 120 subjects from nine hospitals will be included. However, three centers have been deleted because they have not carried out patient recruitment; in addition, we added five centers to hasten the trial. These hospitals include The Second Affiliated Hospital of Shaanxi University of TCM, Xianyang; Zhengzhou Hospital of TCM, Zhengzhou; Hangzhou Hospital of TCM, Hangzhou; The Affiliated Hospital to Changchun University of Chinese Medicine, Changchun; and Zhejiang Hospital of TCM, Hangzhou. The newly added centers have passed the ethical review by the Ethics Committee of Guang’anmen Hospital. To ensure quality, all investigators will receive intensive training regarding the conduct of the research and intervention before recruitment. The flow diagram shown in Fig. 1 provides a brief description of the research process. Our previous protocol defines the sample size calculation [10].

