## Statistical principles

### Overall principles

After completion of the trial, all the statistical analysis tests will use two-sided tests with a nominal alpha level of 0.05, using the SAS [10, 12]. All confidence interval (CI) reports will be 95% CIs. For each outcome, the null hypothesis is the absence of difference between the intervention groups.

The description of measurement indicators will calculate the mean, standard deviation, median, minimum, maximum, and interquartile range (Q3–Q1). Normal continuous variables will be presented as the mean and standard deviation; non-normally distributed continuous variables will be presented as median with interquartile range. Counting indicators will be presented as the frequency and percentage of each category.

Inter-group comparisons will be performed with independent two-sample *t*-tests (normality, homogeneity of variance) or Wilcoxon rank-sum test (non-normality, heterogeneity of variance). Comparisons within normal and nonnormally distributed groups will be performed using paired *t*-test and paired rank-sum test, respectively. *χ*^2^ test or Fisher’s exact probability will be needed for count metrics, and the Wilcoxon rank-sum test will be used for categorical variables. A generalized linear mixed model analysis will be performed on the repeated measured outcome.

In situations where an imbalance in the baseline indicators exists, an adjustment will be required for the efficacy comparison of variables, such as age, sex, and concomitant treatment. The covariance method will be used for continuous variables, and logistic regression analysis was used for count metrics and hierarchical metrics.

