#### Secondary outcome analyses

The secondary outcome of the FAS and PPS will be analyzed, including serum creatinine (SCr, umol/L), eGFR (mL/(min×1.73 m^2^) using CKD-EPI creatinine equation [13]), urinary albumin excretion rate (μg/min), improvement in TCM symptoms, fasting blood glucose (mmol/L), 2-h postprandial plasma glucose (mmol/L), HbA1C (%), cholesterol (mmol/L), triglycerides (mmol/L), high density lipoproteins (mmol/L), low density lipoproteins (mmol/L), blood pressure (mmHg), albumin to creatinine ratio (ACR, mg/g), and the audit of diabetes-dependent quality of life 19 (ADDQoL) [14] The distribution and changes of all the secondary outcomes at the baseline and at each visit point will be compared between and within groups (Table 5).

**Table 5 Tab5:** Secondary outcome analysis

Time point	SZF, number, mean (SD)	Irbesartan, number, mean (SD)	Mean difference (95% CI)	***p*** Value
Scr at	*n* = xx	*n* = xx		
Week 0	xx (xx)	xx (xx)	xx (xx to xx)	.xx
Week 4	xx (xx)	xx (xx)	xx (xx to xx)	.xx
Week 8	xx (xx)	xx (xx)	xx (xx to xx)	.xx
Week 12	xx (xx)	xx (xx)	xx (xx to xx)	.xx
Week 16	xx (xx)	xx (xx)	xx (xx to xx)	.xx
Week 20	xx (xx)	xx (xx)	xx (xx to xx)	.xx
Week 24	xx (xx)	xx (xx)	xx (xx to xx)	.xx
Overall SZF effect ^a^				.xx
eGFR at	*n* = xx	*n* = xx		
Week 0	xx (xx)	xx (xx)	xx (xx to xx)	.xx
Week 4	xx (xx)	xx (xx)	xx (xx to xx)	.xx
Week 8	xx (xx)	xx (xx)	xx (xx to xx)	.xx
Week 12	xx (xx)	xx (xx)	xx (xx to xx)	.xx
Week 16	xx (xx)	xx (xx)	xx (xx to xx)	.xx
Week 20	xx (xx)	xx (xx)	xx (xx to xx)	.xx
Week 24	xx (xx)	xx (xx)	xx (xx to xx)	.xx
Overall SZF effect				.xx
UAER at	*n* = xx	*n* = xx		
Week 0	xx (xx)	xx (xx)	xx (xx to xx)	.xx
Week 4	xx (xx)	xx (xx)	xx (xx to xx)	.xx
Week 8	xx (xx)	xx (xx)	xx (xx to xx)	.xx
Week 12	xx (xx)	xx (xx)	xx (xx to xx)	.xx
Week 16	xx (xx)	xx (xx)	xx (xx to xx)	.xx
Week 20	xx (xx)	xx (xx)	xx (xx to xx)	.xx
Week 24	xx (xx)	xx (xx)	xx (xx to xx)	.xx
Overall SZF effect				.xx
FBG	*n* = xx	*n* = xx		
Week 0	xx (xx)	xx (xx)	xx (xx to xx)	.xx
Week 4	xx (xx)	xx (xx)	xx (xx to xx)	.xx
Week 8	xx (xx)	xx (xx)	xx (xx to xx)	.xx
Week 12	xx (xx)	xx (xx)	xx (xx to xx)	.xx
Week 16	xx (xx)	xx (xx)	xx (xx to xx)	.xx
Week 20	xx (xx)	xx (xx)	xx (xx to xx)	.xx
Week 24	xx (xx)	xx (xx)	xx (xx to xx)	.xx
Overall SZF effect				.xx
2hPG at	*n* = xx	*n* = xx		
Week 0	xx (xx)	xx (xx)	xx (xx to xx)	.xx
Week 4	xx (xx)	xx (xx)	xx (xx to xx)	.xx
Week 8	xx (xx)	xx (xx)	xx (xx to xx)	.xx
Week 12	xx (xx)	xx (xx)	xx (xx to xx)	.xx

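### Secondary outcomes default to unadjusted visit-wise comparisons of available patients, and the planned mixed model is neither given a baseline covariate nor tied to Table 5's differences and CIs

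*Protocol article*

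**What the plan says.** Five parts of the protocol article bear on this.

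- *Overall principles* sets the default test: "Inter-group comparisons will be performed with independent two-sample" t-tests, or the Wilcoxon rank-sum test where normality or equal variance fails. Neither adjusts for baseline.
- The same section adds: "A generalized linear mixed model analysis will be performed on the repeated measured outcome". It names no model terms. It also foresees covariance adjustment, but only if baseline indicators turn out imbalanced, with age, sex and concomitant treatment as examples.
- *Primary outcome analyses* prespecifies ANCOVA with baseline 24-h urinary protein as covariate, because baseline is considered essential for judging progression.
- *Secondary outcome analyses* says: "The distribution and changes of all the secondary outcomes at the baseline and at each visit point will be compared between and within groups". In Table 5 every visit row, week 0 included, has arm means (SD), a mean difference with 95% CI and a p value. The overall-effect row has only a p value.
- *Imputation of missing data* treats the two classes of outcome differently. For the primary outcome, "Multiple imputations will be used for subjects with missing primary outcome data". For secondary and safety outcomes only the actual data are used, and "the missing data will not be imputed nor will the model be adjusted".

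**The concern.** Week-0 values are collected for every Table 5 outcome, yet only the primary outcome is certain to have its baseline value in the model. Readers will take from Table 5 the visit-specific differences and their CIs. The only comparison that the text attaches to single visits is the unadjusted one, made on whoever has a value at that visit.

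If that comparison of levels fills the rows for SCr, eGFR, UAER and ACR, three things follow:

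- chance baseline differences pass into the week-24 difference;
- the CIs are wider than the collected data allow;
- if patients with worsening values leave more often in one arm, the week-24 difference is biased, although those patients' earlier visits are in the database.

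**Working it through.** **Inputs from the article.** "A total of 120 patients with DKD will be equally and randomly divided into two groups", so 60 per arm; "two-sided tests with a nominal alpha level of 0.05". There is no figure to reproduce: the article gives no effect size, SD, power or dropout rate, and on sample size says "Our previous protocol defines the sample size calculation".

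**Assumptions.** Outcome SD = 1 at both times; baseline to week-24 correlation r between 0.3 and 0.9, with 0.6 to 0.8 as the working range; dropout of 10 to 30%. None of these is in the documents.

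**Step 1: precision.** With n = 60 per arm, the standard error (SE) of the week-24 difference is

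- raw levels: sqrt(2/60) = 0.183 SD;
- change scores: 0.183 × sqrt(2(1 − r));
- baseline-adjusted: 0.183 × sqrt(1 − r²).

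The CI width ratio of adjusted to level is therefore sqrt(1 − r²), and of adjusted to change sqrt((1 + r)/2).

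| r | adjusted / level | adjusted / change |
|---|---|---|
| 0.3 | 0.954 | 0.806 |
| 0.5 | 0.866 | 0.866 |
| 0.6 | 0.800 | 0.894 |
| 0.7 | 0.714 | 0.922 |
| 0.8 | 0.600 | 0.949 |
| 0.9 | 0.436 | 0.975 |

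At r = 0.6, 0.7 and 0.8 the adjusted CI is 20%, 29% and 40% narrower than for levels, and about 11%, 8% and 5% narrower than for change scores.

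**Step 2: chance imbalance.** A baseline difference of one SE (0.183 SD) moves the expected week-24 level difference by r × 0.183, that is 0.11 SD at r = 0.6 and 0.15 SD at r = 0.8.

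**Step 3: selective dropout.** A large-sample simulation used three time points (baseline, mid-trial, week 24), equal correlations and no true effect. Dropout in one arm depended on the mid-trial value (logistic slope 1.5 per SD). The other arm had the same dropout rate at random. Absolute bias in the week-24 difference, in SD:

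| r | dropout | observed levels | completers' ANCOVA |
|---|---|---|---|
| 0.6 | 10% | 0.076 | 0.032 |
| 0.6 | 20% | 0.133 | 0.053 |
| 0.6 | 30% | 0.196 | 0.083 |
| 0.8 | 10% | 0.096 | 0.018 |
| 0.8 | 20% | 0.184 | 0.040 |
| 0.8 | 30% | 0.257 | 0.056 |

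A likelihood estimate using all observed visits was within 0.004 SD of zero throughout, and so was the observed-case change score. The change-score result depends on the equal correlations. If selection shifts the mid-trial mean by δ, the week-24 mean shifts by r(mid, 24)·δ and the baseline mean by r(0, mid)·δ, and the two cancel only when those correlations are equal.

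Baseline adjustment alone thus reduces dropout bias of this kind without removing it. Using every observed visit removes it, provided missingness depends only on observed data.

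**The case against.** A reader might infer more than the text supports, in two ways.

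*That Table 5's differences are bound to be unadjusted observed-case comparisons, with the mixed model confined to the overall row.* No sentence says so. These four outcomes are tabulated at seven visits, so the planned mixed model covers them, and such a model can give visit-specific differences and CIs from partial records. The layout settles nothing: Table 4 has the same visit rows and the same empty overall cells for the primary outcome, where ANCOVA and imputation are prespecified.

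*That the statement that "the missing data will not be imputed nor will the model be adjusted" rules out a baseline covariate.* Under a heading on imputation it most naturally means no adjustment for missingness. The baseline point rests instead on *Overall principles* and the two outcome sections.

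Other objections carry weight too. Changes are also to be compared, and against them the precision gain is much smaller. Covariance adjustment is foreseen under imbalance. Model terms and transformations are commonly left to the full SAP. Correlations and dropout are assumed, and the trial is double-blind with double-dummy treatment.

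These points limit the concern but do not remove it. Table 5's week-0 rows show a difference and p value, which only levels can fill, since change at week 0 is zero. The imbalance clause has no threshold, waits for the data, and its examples do not include the outcome's own baseline value. SCr, eGFR, UAER and ACR are not among the variables listed for Table 2. The unadjusted default test, and a baseline covariate named for one outcome only, are stated choices and not omitted detail.

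**Conclusion.** The point holds as a conditional one. The plan's default for secondary outcomes is an unadjusted visit-wise comparison on available patients, and it does not say whether that default or the mixed model produces Table 5's differences and CIs. If the default comparison of levels does, these estimates are less precise than the collected data allow and are exposed to selective dropout.

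For assumed correlations of 0.6 to 0.8, the CI that could be had is 20 to 40% narrower than for raw week-24 levels and about 5 to 11% narrower than for change scores. The simulated level bias of 0.08 to 0.26 SD, against an SE of 0.183 SD with 60 per arm, shows only what selective dropout of the assumed form could do. It is not a forecast, because the article gives no dropout rate or pattern. The primary analysis is not affected. The change is worth making because it costs almost nothing.

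**What to change.** State in *Secondary outcome analyses* that, for each repeatedly measured secondary outcome, Table 5's visit differences and 95% CIs come from the mixed model already planned. Fit it to all observed visits with treatment, visit, treatment-by-visit, baseline value and baseline-by-visit terms. Name the week-24 adjusted difference as the main contrast and drop the separate visit-wise t and Wilcoxon tests. Use a log scale for UAER and ACR if they are skewed.

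In *Imputation of missing data*, add that this analysis uses all observed data without imputation and assumes that missingness depends only on observed data.

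The cost is SAP wording, table footnotes and slightly more modelling work, with no new data or patients. The article reports 100 of 120 patients recruited and blinded statisticians, so a dated change before unblinding is feasible.
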